### **Severity of adverse events**

The severity of clinical AEs is graded on a three-point scale: mild, moderate, severe, and reported on specific AE pages of the CRF.

If the severity of an AE worsens during study drug administration, only the worst intensity should be reported on the AE page. If the AE lessens in intensity, no change in the severity is required.

If an AE occurs during the treatment phase, a new AE page must be filled in with the intensity observed during study drug administration.

#### ***Mild***

Event may be noticeable to subject; does not influence daily activities; the AE resolves spontaneously or may require minimal therapeutic intervention;

#### ***Moderate***

Event may make subject uncomfortable; performance of daily activities may be influenced; intervention may be needed; the AE produces no sequelae.

#### ***Severe***

Event may cause noticeable discomfort; usually interferes with daily activities; subject may not be able to continue in the study; the AE produces sequelae, which require prolonged therapeutic intervention.

A mild, moderate or severe AE may or may not be serious. These terms are used to describe the intensity of a specific event (as in mild, moderate, or severe myocardial infarction). However, a severe event may be of relatively minor medical significance (such as severe headache) and is not necessarily serious. For example, nausea lasting several hours may be rated as severe, but may not be clinically serious. Fever of 39°C that is not considered severe may become serious if it prolongs hospital discharge by a day. Seriousness rather than severity serves as a guide for defining regulatory reporting obligations.

### **Relationship to study drug**

For all AEs, the Investigator will assess the causal relationship between the study drug and the AE using his/her clinical expertise and judgment according to the following algorithm that best fits the circumstances of the AE:

#### ***Unrelated***

- May or may not follow a temporal sequence from administration of the study product
- Is biologically implausible and does not follow known response pattern to the suspect study drug (if response pattern is previously known).
- Can be explained by the known characteristics of the subject's clinical state or other modes of therapy administered to the subject.

#### ***Unlikely***

- There is a reasonable temporal relation between the AE and the intake of the study medication, but there is a plausible other explanation for the occurrence of the AE.

#### ***Possibly***

- The AE has a reasonable temporal relationship with drug administration.
- The AE may equally be explained by the study subject's Clinically state, environmental or toxic factors, or concomitant therapy administered to the study subject.
- The relationship between study drug and AE may also be pharmacologically or clinically plausible.

***Probably***

- There is a reasonable temporal relation between the AE and the intake of the study medication, and plausible reasons point to a causal relation with the study medication.

***Related***

- Reasonable temporal relation between the AE and the intake of the study medication and
- there is no other explanation for the AE and
- subsidence or disappearance of the AE on withdrawal of the study medication and
- recurrence of the symptoms on restart at previous dose (only applies for re-institution of medication).

***Not assessable***

- The causal relationship between the study drug and the AE cannot be judged.

**Reporting procedures**

A special section is designated to adverse events in the case report form. The following details must thereby be entered:

- Type of adverse event
- Start (date and time)
- End (date and time)
- Severity (mild, moderate, severe)
- Serious (no / yes)
- Unexpected (no / yes)
- Outcome (resolved, resolving, not resolved, resolved with sequelae, unknown, fatal)
- Relation to study drug (Related/ Probably/ Possibly/ Unlikely/ Not related/ Not assessable)

Adverse events are to be documented in the case report form in accordance with the above-mentioned criteria.

**Reporting procedures for SAEs**

In case of a serious adverse event, the Investigator has to use all supportive measures for best patient treatment. A written report is also to be prepared and should at least contain the following:

- Patient number
- Patient: sex
- The suspected investigational medical product (IMP)
- The adverse event assessed as serious
- Short description of the event and outcome

If applicable, the initial report should be followed by the Follow up report, indicating the outcome of the SAE. The reports will be submitted to the local ethics-committee, the local authorities (BASG) and to Astra Zeneca (the supplier of the study drug).

### **Reporting procedures for SUSARs**

It must be remembered that the regulatory authorities, and in case of SUSARs which could possibly concern the safety of the study participants, also the Institutional Review Board / Independent Ethics Committee (IRB / IEC) are to be informed. Such reports shall be made by the study management and the following details should be at least available:

- Patient number
- Patient: age in years, sex
- Name of Investigator and investigating site
- Period of administration
- The suspected investigational medical product (IMP)
- The adverse event assessed as serious and unexpected, and for which there is a suspected causal relationship to the IMP
- Concomitant disease and medication
- Short description of the event:
  - Description
  - Onset and if applicable, end
  - Therapeutic intervention
  - Causal relationship
  - Seriousness criteria or reportable reason

Electronic reporting should be the expected method for reporting of SUSARs to the competent authority. In that case, the format and content as defined by the ICH E2A

Guideline should be adhered to. The latest version of MedDRA should be applied. Lower level terms (LLT) should be used.

### **Annual Safety Report**

The Annual Safety Report will be provided by the Investigator at least once a year. This report will also be presented annually to the Independent Ethics (IEC) and to the competent authorities by the sponsor.

## **10. Documentation and data management**

### **Documentation of study results**

A subject screening and enrolment Log will be completed for all eligible or not eligible subjects with the reason for exclusion.

### **Case report form (CRF)**

For each subject enrolled, regardless of study drug initiation, a CRF must be completed and signed by Investigator or a designated sub-Investigator. This also applies to those subjects who fail to complete the study. If a subject withdraws from the study, the reason must be noted on the CRF.

Case report forms are to be completed on an ongoing basis.

CRF entries and corrections will only be performed by study site staff, authorized by the Investigator. All forms should be completed and must be legible. Errors should be crossed out but not obliterated, the correction inserted, and the change initialled, and dated by the Investigator, co-Investigator or study nurse.

The entries will be checked by trained personnel (Monitor) and any errors or inconsistencies will be checked immediately.

The Monitor will collect original completed and signed CRFs at the end of the study. A copy of the completed and signed CRFs will remain on site.

### **Data Collection**

Data collected at all visits are entered into an interactive form. The CRFs will be source documents verified following guidelines established before study onset as detailed in the Monitoring Plan. Maintenance of the study database will be performed by the designated sub-investigators. Each participant will be assigned to a study specific patient number to ensure anonymity.

**Missing, Unused, and Spurious Data**

All available data will be included in the data listings. Complete Case Analysis is performed on only those subjects with a complete set of primary outcome data. Subjects with any missing primary outcome data are excluded from the statistical analysis. Dropouts will be replaced. All data recorded on the CRF will be included in the data listings that will accompany the clinical study report.

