## **6. Withdrawal and replacement of subjects**

### **Criteria for withdrawal**

Subjects may prematurely discontinue from the study at any time. Premature discontinuation from the study is to be understood when the subject did not undergo End of Study (EOS) examination and / or all pivotal assessments during the study.

Subjects must be withdrawn under the following circumstances:

- at their own request
- if the investigator feels it would not be in the best interest of the subject to continue
- if the subject violates conditions laid out in the consent form / information sheet or disregards instructions by the study personal

In all cases, the reason why subjects are withdrawn must be recorded in detail in the CRF and in the subject's medical records. Should the study be discontinued prematurely, all study materials (complete, partially completed and empty CRFs) will be retained.

Replacement policy: Dropouts are not included in the sample size and will be replaced by allocation of the next free subject number.

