### **Follow-up of patients withdrawn from the study**

In case of premature discontinuation after study drug intake, the investigations scheduled for the EOS visit will be performed within 7 days after study drug discontinuation. The subjects will be advised that participation in these investigations is voluntary. Furthermore, they may request that from the time point of withdrawal no more data will be recorded and that all biological samples collected in the course of the study will be destroyed.

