#### **Sample size calculation:**

Up to now there are no studies on hepatic lipid content assessed by H magnetic resonance spectroscopy in patients suffering from autonomous cortisol secretion. Therefore this study has to be considered as a pilot study.

However, evidence from literature and clinical experience suggests that the prevalence of insulin resistance and visceral obesity is increased in this patient population (2). As these factors are both well known to be associated with higher visceral and ectopic fat mass, we estimate that HCL might be about 25% higher in patients with ACS compared to controls. Based on an average HCL of  $5 \pm 2.5$  % fat in a comparable elderly, overweight/obese, sedentary population, which we could observe in our previously

published control population (28) a sample size of 25 patients per group is necessary to detect between group differences to achieve  $\alpha < 0.05$  and  $\beta > 0.80$  in cross-sectional analysis (WPA).

For the interventional part (WPB), we expect a normalization of HCL comparable to the control cohort and therefore a reduction of about 25%. Therefore, a sample size of 15 patients is required to achieve  $\alpha < 0.05$  and  $\beta > 0.80$  in longitudinal analysis.

We expect 2 dropouts in WPA and WPB. These dropouts will be replaced.

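### The complete-case rule drops patients without liver-fat data from the whole analysis, and the protocol does not settle how an early end-of-study scan counts in single-arm WPB

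*Protocol*

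**What the plan says.** Section 10 (Missing, Unused, and Spurious Data) sets a complete-case analysis on the primary outcome and adds: "Subjects with any missing primary outcome data are excluded from the statistical analysis". The same paragraph keeps all recorded data in the listings of the study report.

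Section 6 (Criteria for withdrawal) gives the replacement policy: "Dropouts are not included in the sample size and will be replaced by allocation of the next free subject number". Section 14 (Sample size calculation) repeats it: "We expect 2 dropouts in WPA and WPB. These dropouts will be replaced".

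Three further places bear on patients who stop metyrapone early:

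- Section 6 (Criteria for withdrawal) defines dropout by missed assessments: "Premature discontinuation from the study is to be understood when the subject did not undergo End of Study (EOS) examination", and/or all pivotal assessments.
- Section 6 (Follow-up of patients withdrawn from the study) states that, after stopping, "the investigations scheduled for the EOS visit will be performed within 7 days after study drug discontinuation". It adds: "The subjects will be advised that participation in these investigations is voluntary".
- Section 5 (Working plan B) places the second set of measurements at 12 weeks of treatment.

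Section 7 describes an open-label, single-arm trial. Section 14 (Statistical Analysis) tests the WPB change with paired t-tests. It names no all-treated set and no sensitivity analysis.

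**The concern.** There are two separate problems.

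The first is loss of valid data. HCL is one endpoint among many. Section 4 lists insulin indices, 24-hour blood pressure, inflammation, RAAS activity, thrombin generation, chronotype and other measures that can be complete when liver spectroscopy is not. A rule that removes the patient from the analysis as a whole discards them for no statistical reason, and groups of 25 and 15 have little to spare.

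The second is selection. A before-after comparison without controls has nothing to offset selection on having a second scan. If patients without that scan improved less than the others, the reported fall is too large. Section 8 lists gastrointestinal effects, fatigue, dizziness and adrenal insufficiency as possible drug effects, so stopping for drug-related reasons is plausible, although the protocol gives no rate. Because the status of an early scan is open, who is analysed and who is replaced could also be decided after HCL values are known.

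**Working it through.** **Step 1: reach of the exclusion.** Section 10 uses two terms, the data listings (everything recorded) and the statistical analysis (complete primary outcome only). The second carries no restriction to HCL. Read as written, a WPA patient whose liver spectroscopy fails leaves the glucose-tolerance, blood-pressure and chronobiology comparisons too. The same holds for a WPB patient with no second scan.

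**Step 2: the early stopper.** Take a WPB patient who stops the drug and attends the end-of-study examination within 7 days.

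| Provision | Consequence for this patient |
|---|---|
| Section 5, Working plan B: second measurement at 12 weeks | The early scan is not the planned value, so primary data are missing and the patient is excluded |
| Section 6, Criteria for withdrawal: dropout means missed end-of-study or pivotal assessments | The patient attended, so is arguably not a dropout and not replaced |
| Section 6, Follow-up: end-of-study investigations after stopping, voluntary | A second scan may exist |
| Section 10: exclusion if primary data are missing | Depends on whether the early scan counts, which is not stated |

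Both outcomes, included and not replaced or excluded and replaced, can be defended from the text.

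**Step 3: illustration of size.** The protocol has no figure of its own for this effect. Nor can its WPB sample size of 15 be checked, because the SD of the within-patient change is not given.

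Inputs:

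- 15 analysed patients (Section 14).
- 2 dropouts in WPB. This is an assumption, since Section 14 does not say whether the 2 are per working plan or in total.
- A completer fall of 1.25 points. Section 14 puts HCL in ACS 25% above a control mean of 5, which is 0.25 × 5 = 1.25, and expects a return to the control level.
- The dropouts' change as a fraction f of the completers' fall (assumed).

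Mean fall in all treated = (15 × 1.25 + 2 × f × 1.25) / 17. Overstatement ratio = 17 / (15 + 2f).

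| Assumed change in the 2 dropouts | All-treated fall | Ratio |
|---|---|---|
| Half the completers' fall (f = 0.5) | 20.00 / 17 = 1.18 | 17/16 = 1.06 |
| No change (f = 0) | 18.75 / 17 = 1.10 | 17/15 = 1.13 |
| Worsening by half that amount (f = −0.5) | 17.50 / 17 = 1.03 | 17/14 = 1.21 |

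The ratio does not depend on the size of the fall. With 5 dropouts and no change it is 20/15 = 1.33, a fall of 18.75 / 20 = 0.94.

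**Step 4: scale against sampling error.** Fifteen pairs give 80% power for 1.25 points only if the SD of change is at most about 1.61. The standard error is then 1.61 / √15 = 0.42. The no-change shift of 1.25 − 1.10 = 0.15 is about one third of it.

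**The case against.** A reader might infer that the liver-fat effect is estimated only in patients who tolerate metyrapone. The text does not support that. Dropout is defined by missed assessments, not by stopping the drug, and early stoppers are offered an end-of-study scan that may keep them in the complete-case set. The supportable statement is that the analysed set is mainly completers, with the status of early stoppers unsettled.

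A reader might also infer that replacement hides how many patients could not take the drug, so that 2 stopping among 17 (11.8%, exact 95% CI 1.5% to 36.4%) would be reported as 0 of 15. That is not shown either. Section 6 requires withdrawal reasons in the CRF, and a replacement takes a new subject number. Section 10 (Case report form) requires a form for every enrolled subject and adds: "This also applies to those subjects who fail to complete the study". Section 9 requires adverse-event reporting, and Section 10 lists all recorded data. No provision uses completers as the denominator for tolerability. A safety set may be defined in an analysis plan that was not available here.

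It is also fair that this is a pilot described as exploratory, that the size rests on assumed changes in dropouts, and that the shift is small beside sampling error.

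What remains is that the exclusion is a rule fixed in the protocol, not a detail left for later. An analysis plan with per-endpoint or all-treated sets would contradict its wording. The loss of secondary data does not depend on any assumption about dropouts.

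**Conclusion.** The point holds as a defect of moderate severity. The exclusion reaches beyond HCL, so valid secondary data are discarded in WPA and WPB for every patient without usable liver spectroscopy. In WPB the paired HCL change comes mainly from completers, and Sections 5, 6 and 10 do not settle how an early end-of-study scan is treated.

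The 6% to 21% range is an illustration. It assumes 2 WPB dropouts with no usable second scan and a change in them between half the completers' fall and a worsening of the same half size. Dropouts who did as well as completers would produce no bias. The documents establish neither a biased result nor concealed tolerability data.

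**What to change.** 1. In Section 10, limit the exclusion to the endpoint whose data are missing.
2. Reconcile Section 5 (Working plan B), both Section 6 passages and Section 10, before data are seen, on whether an early end-of-study scan is a post-treatment value and whether that patient is replaced.
3. Keep the 12-week paired analysis as the main WPB analysis, since it matches the stated aim. Add a sensitivity analysis of all treated patients with a baseline scan, using the early scan where there is one and assuming no change where there is no second scan.
4. State that the exclusion does not apply to adverse-event and discontinuation summaries, which use everyone who took at least one dose. Report the number replaced, with reasons.

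Replacement itself can stay, and no extra data collection is needed. The cost is some rewording and one or two additional analysis runs. The drawback is that early scans reflect shorter exposure and may dilute the estimate, which is why they belong in the sensitivity analysis and not in the main one.

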**Safekeeping**

The Investigator will maintain adequate and accurate record to enable the conduct of the study to be fully documented and the study data to be subsequently verified (according to ICH-GCP “essential documents”). These documents will be classified in two different categories: Investigator`s file, and subject clinical source documents.

The Investigator`s file will contain the protocol/amendments, EudraCT forms, CRFs (eCRF printout), standard operation procedures (SOPs), data clarification and query forms, EC/IRB and Health Authority approval with correspondence, informed consent, drug records, staff curriculum vitae and authorization forms, screening and enrolment logs, and other appropriate documents/correspondence as per ICH/Good Clinical Practice (GCP) and local regulations. Subject clinical source documents include, but are not limited to subject hospital/ clinic record, physician`s and nurse`s notes, appointment book, original laboratory reports, ECG, X-ray, pathology and special assessment reports, consultant letters, etc.

These two categories of documents must be kept on file by the Investigator for as long as needed to comply with national and international regulations (in Austria 15 years after discontinuing clinical development or after the last marketing approval). If source documents are not durable as long as needed (e.g. ECG printouts) they must be preserved as a copy. No study document should be destroyed without prior written approval from the Department of Internal Medicine III, Division of Endocrinology and Metabolism.

When source documents are required for the continued care of the subjects, appropriate copies should be made for storing outside of the site.

**Periodic Monitoring**

Periodic monitoring will be performed by trained personal from the Medical University of Vienna, who will not be involved in any other study related activities. The designated monitor ([name]) will contact and visit the Investigator regularly and will be

allowed to have access to all source documents needed to verify the entries in the CRFs and other protocol-related documents provided that subjects confidentiality is maintained in agreement with local regulations. It will be the monitor's responsibility to inspect the CRFs at regular intervals according to the monitoring plan throughout the study to verify the adherence to the protocol and the completeness, consistency and accuracy of the data being entered on them. The monitoring standards require full verification for the presence of informed consent, adherence to the inclusion/exclusion criteria, documentation of SAEs and the recording of the main efficacy, safety and tolerability endpoints.

The monitor will be working according to SOPs and will provide a monitoring report after each Visit for the sponsor. Depending on the quality of the data, additionally monitoring visits may be necessary according to the sponsor's discretion. The Investigator will resolve discrepancies of the data.

### **Audit and Inspections**

Upon request, the Investigator will make all study-related source data and records available to competent authority inspectors. The main purposes of an audit or inspection are to confirm that the rights and the welfare of the subjects have been adequately protected, and that all data relevant for safety and efficacy of the investigational product have appropriately been reported to the sponsor.

## **11. Ethical and Legal Aspects**

### **Informed consent of subjects**

Following comprehensive instruction regarding the nature, significance, impact and risks of this clinical trial, the patient must give written consent to participation in the study.

During the instruction the trial participants are to be made aware of the fact that they can withdraw their consent – without giving reasons – at any time without their further medical care being influenced in any way.

In addition to the comprehensive instructions given to the trial participants by the Investigator, the trial participants also receive a written patient information sheet in comprehensible language, explaining the nature and purpose of the study and its progress.

The patients must agree to the possibility of study-related data being passed on to relevant authorities.

The patients must be informed in detail of their obligations in relation to the trial participants insurance in order not to jeopardize insurance cover.

